### Assessments

Serum PSA will be assessed, and PSMA PET/CT imaging will be performed once every 3 cycles during the systemic treatment [27]. If serum PSA level increases or patients suffer from osteodynia, chest, abdominal, and pelvic CT/MRI imaging will be performed. The participants will be followed up via telephone until the end of the study, death, or loss to follow-up, within ± 4 weeks (Table 1). ^68^Ga or ^18^F can be used as a tracer and the type of tracer for each patient will remain unchanged throughout the study.

**Table 1 Tab1:** Participant timeline

	Screening Period		Observation and Treatment Period											Group Exit Confirmation	Follow-up Period
Item	Within 14 days before first dosing	Within 7 days before first dosing	1st cycle	2nd cycle	3rd cycle		Planned surgery date (First 7 ± 1 days)	Surgery date	After surgery date (14 ± 3 days)	4th cycle	5th cycle	6th cycle	6th cycle	Group-exit investigation & observation confirmation	Safety & survival follow-up
			C1D1 (± 3 days)	C2D1 (± 3 days)	C3D1 (± 3 days)	C3D28 (± 3 days)				C4D1 (± 3 days)	C5D1 (± 3 days)	C6D1 (± 3 days)	C6D28 (± 3 days)	C6D28 + 30 (± 7 days)	Once every 3 m in 1st–2nd y; once every 6 m in 3rd y
Signing of informed consent [1]	√														
Demographic characteristics and history of tumor or other diseases [2]	√														
Vital signs [3]		√				√	√						√	√	
Physical examination [4]		√													
ECOG scoring [5]		√				√							√	√	
Testosterone examination [6]	√														√
Blood routine [7]		√													
Urine routine [8]		√													
Occult blood in stool [9]		√													
Blood biochemistry [10]		√													
Blood coagulation function [11]		√													
HIV, Hepatitis B, Hepatitis C [12]	√														
12-lead electrocardiogram [13]		√													
Ultrasonic cardiogram [14]	√														
Prostate specimen examination [15]	√							√							
PSA examination [16]		√				√							√	√	√
Imaging examination [17]	√												√		√
Bone scan [18]													√		√
PSMA-PET [19]	√					√									√
Metastasis-directed therapy [20]										√					
Systemic therapy drug compliance [21]						√							√	√	
Concomitant drug/therapy [22]	√													√	
Adverse event recording [23]						√							√	√	
Progressing event, survival state, and subsequent tumor treatment [24]														√	√

Description:

a: Medical and treatment history, including present and past medical history, history of surgery and allergy, and history of anticancer therapy (chemotherapy/radiotherapy/targeted therapy/hormone therapy/surgery)

b: Vital signs, including temperature, respiration, pulse, and blood pressure

c: Physical examination, including height and weight measurements, and assessments of the general body surface, skin, head and neck, chest, abdomen, limbs, nervous system, and lymph nodes. Height will be measured only in the screening period, not during other visits and interviews

d: Laboratory examinations:

➢ In case the interval between the laboratory examination and the examination on the 1^st^ day of the 1^st^ week in the screening period is less than 7 days, the examination will not be performed on the first day of the first week

➢ Blood routine test evaluating red blood cell (RBC), white blood cell (WBC), hemoglobin (HGB), platelet (PLT), and differential counts of white blood cells (basophil count, BASO#; eosinophil count, EO#; lymphocyte count, LYMPH#; monocyte count, MONO#; neutrophil count, NEUT#; neutrophil percentage, NEUT%)

➢ Blood biochemical analysis detecting alanine aminotransferase (ALT), aspartate aminotransferase (AST), alkaline phosphatase (ALP), glutamyl transpeptidase (GGT), total bilirubin (TBIL), urea nitrogen (BUN)/urea (UREA), serum creatinine (SCr), potassium (K), sodium (Na), chlorine (Cl), magnesium (Mg), calcium (Ca), phosphorus (P), glucose (GLU), triglyceride (TG), total cholesterol (TC), low-density lipoprotein (LDL-C), high-density lipoprotein (HDL-C), and albumin (ALB)

➢ Urine routine detecting urine pH, urine protein (U-PRO), urine glucose (U-GLU), urinary white blood cell (U-WBC), and urinary red blood cell (U-RBC)/hematuria

➢ Coagulation function (during screening and at the end of treatment) will be assessed by determining prothrombin time (PT), activated partial thromboplastin time (APTT), fibrinogen (FIB), thrombin time (TT), and international normalized ratio (INR)

e: Prostate specimen examination: Puncture biopsy specimen, liquid biopsy specimen, or paraffin section specimen of the prostate will be collected to detect prostate-cancer-related biomarkers

f: After 6 cycles of treatment, the investigators will determine if PSMA PET/CT examination is needed

g: After 3 cycles of treatment, a patient with elevated serum PSA level and ostalgia will undergo conventional imaging examination (bone scan, and CT/MRI of the chest, abdomen, and pelvic cavity)

h: Adverse events and drug combinations: From the signing of informed consent to 30 days after the last study drug administration, the adverse events (including severe adverse events) and drug combinations will be recorded

### Data management

This trial will use case report forms (CRF) to collect basic and clinical data. The investigators will maintain source files for each subject, including original medical records and other written data or records. The data entered from the CRF must be linked to source files for each subject. Data managers will write the data review reports following the trial protocol and data review criteria from databases. Primary investigators, statisticians, and data managers will attend the data review meetings, and the data will be reviewed, resolved, and signed by the representatives attending the meetings. After all personnel approve the data, data managers will organize and execute data-locking tasks. The locked data will be submitted to statisticians for statistical analysis.

### Monitoring

An independent data and safety monitoring committee will be established to assess safety when serious adverse events occur. All adverse events will be recorded. A qualified independent auditor will be appointed to scrutinize all trial protocols, and the trial will be conducted before and during the treatment period based on a written procedure.

### Statistical analysis

The primary endpoint is the rate of participants with an undetectable PSA after 6 cycles of the apalutamide plus ADT. Fleming's two-stage group sequential design will be employed in this study, where the null hypothesis is that the rate of participants with an undetectable PSA will be ≤ 40%, and the alternate hypothesis was an undetectable PSA of > 60%. The test will be one-sided, with an α of 0.05 and a power value of 0.80. The first stage of the study will enroll 21 patients; if the number of patients with undetectable PSA is ≤ 8 during this stage, this treatment strategy will be considered ineffective and the study will be terminated. In case the number of patients with undetectable PSA is > 8 at the initial stage, this study will enter its second stage, when more patients will be added to reach the sample size of 42. If the number of patients with undetectable PSA is ≤ 22 during this period, this protocol will be considered ineffective. With an assumption of a dropout rate of 10%, a total of 47 patients will be needed for the effective analysis.

The full analysis set (FAS) will be used for efficacy analysis. The FAS follows the intend-to-treat (ITT) principle, where patients receiving at least one treatment are included in the analysis. The safety analysis set will include all patients receiving at least one treatment in this study, using the safety records after the treatment.

Quantitative data with normal distribution or near normal distribution will be expressed as mean ± standard deviation; those with skewed distribution or heterogeneity of variance will be expressed as median and quartile. Categorical data will be expressed as numbers and percentages. Categorical data will be analyzed by chi-square test or Fisher's exact test. The Kaplan–Meier method will be used to calculate the median times (95% confidence intervals) for time-to-event variables and generate survival plots. Each variable will be analyzed against the baseline value of the screening period. Paired t-test, χ2-test, exact probability method, or non-parametric test will be utilized to assess the differences of determinants before and after the study.

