**Methods:**

CHAMPION (NCT05717582) is an open-label, single-arm, phase II trial, planning to enroll newly diagnosed mHSPC cases with oligometastases (≤ 10 distant metastatic sites in conventional imaging). Patients will receive 6 cycles of apalutamide plus ADT. Patients with oligometastatic disease at PSMA PET/CT after 3 treatment cycles will receive cytoreductive radical prostatectomy. PSMA PET/CT-guided metastasis-directed external radiation therapy will be determined by the investigators. Apalutamide plus ADT will be continued for 2 weeks postoperatively. The primary endpoint is the proportion of patients with undetectable prostate-specific antigen (PSA), no disease progression, and no symptom deterioration after 6 cycles of apalutamide plus ADT. Secondary endpoints include the percentage of patients with PSA ≤ 0.2 ng/mL and oligometastases by the end of 3 treatment cycles, PSA response rate, and safety. Fleming’s two-stage group sequential design will be adopted in the study, where the null hypothesis is that the rate of patients with an undetectable PSA is ≤ 40% after 6 cycles of treatment, while the alternate hypothesis is an undetectable PSA of > 60%; with one-sided α = 0.05, power = 0.80, and an assumed dropout rate of 10%, the required number of patients for an effective analysis is 47. Enrolment in the study commenced in May 2023.

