**Fig. 1 Fig1:**
[figure not shown]
The flowchart of the proposed trial. MDT: metastasis-directed therapy; cRP: cytoreductive radical prostatectomy; ECOG PS: Eastern Cooperative Oncology Group Performance Status; RT: radiation therapy; ADT: androgen deprivation therapy; PSMA-PET/CT: prostate-specific membrane antigen positron emission tomography/computed tomography; PSA: prostate-specific antigen; CTCAE: Common Terminology Criteria for Adverse Events

The primary endpoint is the proportion of patients with undetectable prostate-specific antigen (PSA), no disease progression, and no symptomatic deterioration after 6 treatment cycles. Undetectable PSA is defined as ≤ 0.2 ng/mL and confirmed by two successive evaluations at least 3 weeks apart. Disease progression will be evaluated by a blinded independent central review (ICR) according to the Response Evaluation Criteria in Solid Tumours (RECIST) version 1.1. Symptomatic deterioration is referred to as a situation where the treatment needs to be interrupted, but with no apparent disease progression.

The secondary endpoints include the following:Percentage of cases with undetectable PSA after 3 treatment cycles.PSA50 and PSA90 response rate after 3 and 6 treatment cycles. PSA50 and PSA 90 response rate are the percentages of patients who have a reduction of greater than 50% and 90% from baseline, respectively.Comparisons of baseline conventional imaging and PSMA PET/CT imaging features, including tumor-node-metastasis (TNM) staging, molecular imaging TNM (miTNM) classification, number of metastases, and metastatic sites.Proportion of patients with ≤ 10 metastases (except pelvic lymph node metastases without new metastases) assessed by PSMA PET/CT at the end of cycle 3.Comparison of conventional imaging and PSMA PET/CT imaging features at the end of the 3 and 6 treatment cycles, including change in prostate volume, number and volume of prostate tumor nodules, distribution of metastatic lesions and number of metastatic lesions.Safety assessment: including adverse events (graded according to National Cancer Institute's Common Terminology Criteria for Adverse Events 5.0 criteria) and surgical complications (graded according to Clavien-Dindo classification).Assess the feasibility of implementing cRP ± MDT based on the number of metastases in PSMA PET/CT.

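### The primary endpoint is a three-part composite where it is defined, but PSA alone in the hypotheses and both stage cut-offs

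*Protocol article*

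**What the plan says.** The endpoint paragraph of the Trial overview (after Fig. 1) reads: "The primary endpoint is the proportion of patients with undetectable prostate-specific antigen (PSA), no disease progression, and no symptomatic deterioration after 6 treatment cycles". The abstract's Methods paragraph gives the same three parts.

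The Trial overview then defines each part separately:
- **Undetectable PSA:** at or below 0.2 ng/mL, "confirmed by two successive evaluations at least 3 weeks apart".
- **Progression:** blinded independent central review under RECIST 1.1.
- **Symptomatic deterioration:** "Symptomatic deterioration is referred to as a situation where the treatment needs to be interrupted, but with no apparent disease progression".

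The Statistical analysis section opens differently: "The primary endpoint is the rate of participants with an undetectable PSA after 6 cycles of the apalutamide plus ADT". It continues that "the null hypothesis is that the rate of participants with an undetectable PSA will be ≤ 40" per cent, sets the alternative above 60% on the same quantity, and counts patients with undetectable PSA in both rules: stop if 8 or fewer of the first 21, and ineffective if 22 or fewer of 42. The abstract also pairs the composite endpoint with PSA-only hypotheses, within one paragraph.

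**The concern.** The two definitions classify some patients differently. Someone with confirmed PSA at or below 0.2 ng/mL whose disease progresses on central review fails the composite but counts towards the 9 and 23 responders needed to pass the two stages. The composite rate can never exceed the PSA rate, so any error runs in a known direction:

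- If PSA responders are counted and the result is reported as the composite primary endpoint, the chance of a false positive rises.
- If composite responders are counted against a 60% target chosen for PSA alone, power falls below the stated 0.80.

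These harms are alternatives; only one can occur. The trial is single-arm, open-label and already enrolling, so while the definition is open the choice could be made with outcome data in view. The stage 1 stopping decision also needs one definition before it is taken.

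**Working it through.** **Inputs (Statistical analysis section).** Null rate 0.40, alternative 0.60, one-sided α 0.05, power 0.80. Stage 1: 21 patients, continue if more than 8 respond. Final: 42 patients, ineffective if 22 or fewer respond, so 23 or more is taken as success. No early stop for efficacy is stated. Dropout 10%, total 47.

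**Step 1: reproduce the plan.** With X₁ ~ Bin(21, p) and X₂ ~ Bin(21, p), independent,

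P(success | p) = Σ from x = 9 to 21 of P(X₁ = x) · P(X₂ ≥ 23 − x).

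- At p = 0.40: 0.0367, within the 0.05 limit.
- At p = 0.60: 0.7976, against the stated 0.80.
- Dropout: 42 / 0.9 = 46.7, rounded up to 47, as stated.

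The design is correctly sized for one binary endpoint with rates of 40% and 60%.

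**Step 2: separate the two endpoints.** Let f be the share of patients with undetectable PSA who fail on progression or symptomatic deterioration. Then composite rate = PSA rate × (1 − f). The documents give no value for f, so it is an assumption, shown from 0 to 20%.

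- *Case A: composite truly at its 40% null, PSA alone counted.* The PSA rate is 0.40 / (1 − f). For f = 10%: 0.40 / 0.90 = 0.444, and P(success | 0.444) = 0.115.
- *Case B: PSA rate 60%, composite counted.* The composite rate is 0.60 × (1 − f). For f = 10%: 0.60 × 0.90 = 0.54, and P(success | 0.54) = 0.518.

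| f | Case A: PSA rate | Case A: P(success) | Case B: composite rate | Case B: power |
|---|---|---|---|---|
| 0% | 0.400 | 0.037 | 0.600 | 0.798 |
| 1% | 0.404 | 0.041 | 0.594 | 0.774 |
| 2% | 0.408 | 0.046 | 0.588 | 0.750 |
| 3% | 0.412 | 0.052 | 0.582 | 0.724 |
| 5% | 0.421 | 0.066 | 0.570 | 0.669 |
| 10% | 0.444 | 0.115 | 0.540 | 0.518 |
| 15% | 0.471 | 0.196 | 0.510 | 0.365 |
| 20% | 0.500 | 0.317 | 0.480 | 0.231 |

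In case A the 0.05 limit is crossed between f = 2% and f = 3%.

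**The case against.** The best reply is that undetectable PSA in the Statistical analysis section is shorthand for the composite. The abstract states the composite and then the PSA-only hypotheses in the same paragraph, as a condensed article might, and the full protocol and SAP are not shown. However, the Trial overview gives undetectable PSA its own definition, separate from the other two components, and uses it in that narrow sense for the 3-cycle secondary endpoint. Nowhere is it said to stand for the composite. An unseen SAP may choose one reading, but the published text would still contradict itself.

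Three further points stand in part:
- **Which text governs.** If the Statistical analysis section governs, its rule matches its own endpoint. The defect is then that two primary endpoints are stated, with nothing to say which prevails.
- **Size.** It depends on an assumed f. At 1% or 2% the false-positive probability is 0.041 or 0.046, still under 0.05, and power is 0.77 or 0.75.
- **The deterioration example.** A patient whose treatment is interrupted before 6 cycles are complete is not clearly a responder under the statistical text, which counts PSA after 6 cycles. The example of progression on central review has no such doubt.

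**Conclusion.** The concern holds. The article states two incompatible primary endpoints, and the hypotheses and both stage rules rest on the narrower one, while the abstract and the Trial overview promise the composite. The sample size is not miscalculated; what is unsettled is which endpoint the 40% and 60% rates and the cut-offs of 8 and 22 belong to.

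The numerical consequence is conditional on f. It is small up to about 2%. From 5% to 15% it is material: a false-positive probability of 0.066 to 0.196 if PSA alone is counted with the composite at 40%, or power of 0.67 to 0.36 if the composite is counted with the PSA rate at 60%. These figures assume independent patients, 42 evaluable, and success at 23 or more. Whatever f is, this must be settled, because it decides who counts as a responder in the go/no-go rule.

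**What to change.** Use the composite from the Trial overview throughout the Statistical analysis section and the abstract:

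1. State the null and alternative as composite rates (40% versus 60%).
2. Count composite responders at both stages, and say explicitly that 23 or more of 42 is success.
3. Make undetectable PSA alone at 6 cycles a named secondary endpoint.
4. Confirm that 60% was meant for the composite. If it was chosen for PSA alone, restate the power at the lower composite rate expected.

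Naming PSA alone as primary everywhere and moving the other two components to secondary endpoints would also end the contradiction, but it would give up the endpoint that the article defines in full.

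**Cost.** No new data collection is needed, but this is more than an edit to the text. It is an amendment to an enrolling trial, and it should record what outcome data had been seen and whether the stage 1 count had been made. Ideally it precedes that count. Under the composite, somewhat fewer patients may count as responders, or the stated power may have to be less favourable.

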
### Study treatment

Patients will receive apalutamide in combination with ADT. Each treatment cycle will be 28 days, with a total of 6 treatment cycles. Apalutamide will be given orally at a dosage of 240 mg once daily, but this dose will be adjusted according to the instruction in case of intolerability [26]. The ADT regimen consists of a gonadotropin-releasing hormone analog (GnRHa), either a GnRHa agonist or a GnRHa antagonist. The type, frequency, and dosage of the ADT will be determined by the investigators, and the dosage will be adjusted according to the instruction if adverse events occur.

The PSMA PET/CT imaging will be performed in a 2-week window after 3 cycles of apalutamide plus ADT. Based on the PSMA PET/CT images, the investigators will decide on subsequent cytoreduction. The patients with ≤ 10 distant metastatic sites by PSMA PET/CT, will be treated with cRP with/without MDT. cRP and PLND will be performed based on the evaluation of preoperative PSMA PET/CT images. ADT will be maintained during the whole perioperative period, while apalutamide will be discontinued for at least 1 week before the day of surgery. Apalutamide plus ADT will be restored 2 weeks postoperatively based on the evaluation by investigators. A multidisciplinary team including investigators will reach a decision on the application of MDT. SBRT will be performed and the dosages for different body sites will vary based on the tolerance level of the organ with metastases and the surrounding normal tissue. The lesions will be exposed to radiation with a recommended protocol using guidelines and the clinical experience of the investigators. The patients will be concurrently administered apalutamide plus ADT during the radiotherapy. For patients undergoing cytoreduction (cRP with/without MDT), the entire treatment duration will not exceed 8 months.

Cases recovering from the oligometastatic state after three cycles of apalutamide plus ADT assessed by PSMA PET/CT imaging will continue to receive apalutamide plus ADT. Treatment will be terminated if the patients cannot benefit from the therapy, experience intolerant toxicity, or withdraw the informed consent. For patients who discontinue apalutamide treatment plus ADT within the first three months of the trial, subsequent treatment will be determined by the investigators.

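### The 10% dropout allowance is added to the total (42 to 47) but not to the 21-patient stage 1, so read literally the futility stop is stricter than the design intended

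*Protocol article*

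**What the plan says.** All the design figures are in the Statistical analysis section of the protocol article.

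- Hypotheses: "the null hypothesis is that the rate of participants with an undetectable PSA will be ≤ 40" per cent, and "the alternate hypothesis was an undetectable PSA of > 60" per cent.
- Error rates: "The test will be one-sided, with an α of 0.05 and a power value of 0.80".
- Stage 1: "The first stage of the study will enroll 21 patients; if the number of patients with undetectable PSA is ≤ 8 during this stage", the strategy is declared ineffective and the study ends. With more than 8, enrolment continues to 42.
- Final analysis: 22 or fewer responders means ineffective, so success needs at least 23.
- Dropout: "With an assumption of a dropout rate of 10%, a total of 47 patients will be needed for the effective analysis". No matching figure is given for stage 1, and the 21 are not described as evaluable.
- Analysis set: the full analysis set follows intention to treat, "where patients receiving at least one treatment are included in the analysis".

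The Trial overview section defines undetectable PSA as a value of at most 0.2 ng/mL, confirmed at two evaluations at least 3 weeks apart. A patient lost before the cycle-6 PSA therefore cannot add to the responder count.

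**The concern.** The two sample sizes in the stopping rule, 21 and 42, belong to one design without dropout. The plan then converts 42 to an enrolment figure, 47, and leaves 21 as it stands, described by the verb enrol. If that wording is followed, the plan's own 10% rate means that about 2 of the 21 (21 × 0.10 = 2.1) will have no cycle-6 result at the look, while the cut-off stays where 21 complete results would put it.

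This matters because the stage-1 stop ends the trial. A shortfall at the final analysis can be weighed against the estimate and its interval. A trial closed at stage 1 gives no such opportunity. The protection against dropout was given to the total but not to the step that decides whether the total is ever reached.

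**Working it through.** **Inputs** (Statistical analysis section): p0 = 0.40, p1 = 0.60, stage 1 of 21 with a stop at ≤ 8, total 42 with success at > 22, dropout 10%, inflated total 47.

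**Formulas.** With n1 patients in stage 1, n in total and response probability p:

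- P(stop) = P(Bin(n1, p) ≤ 8)
- P(success) = Σ over x = 9…n1 of P(Bin(n1, p) = x) × P(Bin(n − n1, p) > 22 − x)

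**Step 1: the plan's own design, no dropout (21 then 42).**

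- Type I error at 0.40: 0.037
- Power at 0.60: 0.798
- P(stop) at 0.60: 0.035
- P(stop) at 0.40: 0.524

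The stated 0.05 and 0.80 are reproduced. So 21 and 42 are both numbers before dropout, and 42/0.9 = 46.7 rounds up to the stated 47.

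**Step 2: the text taken literally, with 10% dropout unrelated to response.** The chance that an enrolled patient counts as a responder is 0.60 × 0.90 = 0.54 under the alternative and 0.40 × 0.90 = 0.36 under the null.

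| Stage 1 / total enrolled | P(stop), evaluable rate 60% | Power | P(stop), evaluable rate 40% | Type I error, evaluable rate 40% |
|---|---|---|---|---|
| 21 / 47 (as written) | 0.107 | 0.764 | 0.671 | 0.042 |
| 24 / 47 | 0.034 | 0.795 | 0.484 | 0.046 |

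The ratio of stop risks as written is 0.107/0.035, about 3.0. The stop is a fixed count, so 0.107 is the same whether dropouts are scored as non-responders or left out: neither adds to the count.

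**Step 3: exactly 2 of 21 lost.** P(Bin(19, 0.60) ≤ 8) = 0.088, about 2.5 times 0.035. With 42 evaluable in total, power is 0.776.

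**Step 4: where the shortfall comes from.** With 47 enrolled and no interim look, P(Bin(47, 0.54) > 22) = 0.8005. The allowance works for the total, and the fall to 0.764 (3.7 points) comes from the stage-1 stop.

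**Step 5: sensitivity to the dropout assumption (21 of 47 enrolled).**

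- Half of the dropouts already count as failures within the 60%: p = 0.60 × 0.95 = 0.57, P(stop) = 0.064, power 0.866.
- The 60% already includes all dropouts: p = 0.60, P(stop) = 0.035, power 0.933.

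**The case against.** The strongest answer is that 21 and 42 sit on one scale, that the inflation to 47 comes afterwards, and that a condensed article used the word enrol loosely for both stages. If 21 means evaluable, there is no loss. That is a fair reading, and Step 1 is consistent with it. But the text does not say so, and "The first stage of the study will enroll 21 patients" is the operative wording for the stop.

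A second answer is that 0.54 may count failures twice. The Study treatment section says "Treatment will be terminated if the patients cannot benefit from the therapy, experience intolerant toxicity, or withdraw the informed consent". The Trial overview section makes progression and symptomatic deterioration, the latter meaning that treatment has to be interrupted, failures of the primary endpoint. Some patients who leave treatment may therefore already be among the 40% of non-responders. This stands, and it is why the result is conditional. Step 5 shows how quickly the effect shrinks.

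Third, not every wrong stop costs a success. P(stop) is 10.7%, but removing the stop raises power by only 3.7 points, so about two thirds of the stopped trials would have failed at the end anyway. This also stands.

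A reader might infer more than the document supports:

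- **That the stop risk certainly triples and power is certainly missed.** Both need the literal reading of enrol and dropout wholly outside the endpoint.
- **That the plan leaves dropouts unscored.** The intention-to-treat sentence points to non-response, and detailed missing-data rules may sit in the full protocol or analysis plan, which are not shown.
- **That 23 enrolled would be enough.** 21/0.9 = 23.3, and the plan rounds up. With 23 enrolled, 21 or more are evaluable only 59% of the time (P(Bin(23, 0.9) ≥ 21)).

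**Conclusion.** The point holds in a limited, conditional form: the dropout allowance and the stage-1 number are on different scales as written. The loss is a wrong-stop risk of about 9–11% instead of 3.5%, and power of about 0.76–0.78 instead of 0.80. It rests on three assumptions: 21 means enrolled, 60% is a rate among evaluable patients, and the 10% dropout is unrelated to response and spread evenly over both stages. The plan's own inflation to 47 supports the second, since an all-enrolled rate of 60% would need no inflation. The document does not settle the first or the third. The stated design without dropout is not in error.

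The type I error figures for 47 enrolled hold only if the 40% null is also a rate among evaluable patients. How the final cut-off of 22 relates to a denominator of 47 is a separate matter, not judged here.

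**What to change.** Put stage 1 on the same scale as the total, in one sentence of the Statistical analysis section, before the stage-1 data are read. Either of two rules would do. They are not identical, so one should be chosen.

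1. Make the stage-1 look on the first 21 patients evaluable for the cycle-6 endpoint, with the stop at ≤ 8. This restores the designed stop risks (0.035 at 60%, 0.524 at 40%). The number enrolled by then will vary.
2. State that stage 1 enrols 24 patients (21/0.9 = 23.3, rounded up as was done for 47), with the stop at ≤ 8 and the total kept at 47. This gives a stop risk of 0.034, power 0.795 and type I error 0.046 at an evaluable null rate of 40%.

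If stage 1 is to stay at 21 enrolled, restate power as about 0.76. If 21 was always meant as evaluable, option 1 simply records that.

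Cost: total enrolment is unchanged. Under option 2, 3 more patients enter before a justified futility stop (24 against 21), and the chance of stopping early at an evaluable rate of 40% falls from 67% to 48%. The design without dropout has 52%, so the look returns to roughly its intended behaviour.

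### The final cut-off of more than 22 responders is calibrated for 42 patients, but the plan treats 47 and analyses all treated patients; alpha could reach 12%

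*Protocol article*

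**What the plan says.** All the elements stand in the Statistical analysis section of the Protocol article.

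- Hypotheses: "the null hypothesis is that the rate of participants with an undetectable PSA will be ≤ 40" per cent, and "the alternate hypothesis was an undetectable PSA of > 60" per cent.
- Error rates: "The test will be one-sided, with an α of 0.05 and a power value of 0.80".
- Stage 1: "The first stage of the study will enroll 21 patients"; the study stops if 8 or fewer respond.
- Stage 2: otherwise "this study will enter its second stage, when more patients will be added to reach the sample size of 42"; 22 or fewer responders means ineffective.
- Inflation: "With an assumption of a dropout rate of 10%, a total of 47 patients will be needed for the effective analysis". The Abstract (Methods) repeats the figure: "the required number of patients for an effective analysis is 47".
- Analysis set: efficacy is analysed in the FAS, described as following the intention-to-treat principle, "where patients receiving at least one treatment are included in the analysis".

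The article gives no cut-off for a number other than 42, and no rule that limits the test to 42 of the treated patients.

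**The concern.** Inflating 42 to 47 makes sense if about five patients drop out of the analysis and leave 42. The FAS definition removes only patients who were never treated. Dropouts after the first dose stay in, so the analysed number can be anything up to 47, while the only cut-off given belongs to 42.

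A fixed count is easier to reach with more patients. Using >22 on a larger FAS therefore raises the chance of declaring success when the true rate is only 40%. With 47 in the FAS, success would be declared at 23/47 = 48.9%, where the exact one-sided 95% lower bound is 36.2%, below the null value.

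This is the trial's only formal efficacy decision. As written, a result of 23 or 24 responders among 47 could be called a success or a failure depending on a choice made after the data are seen.

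**Working it through.** **Inputs** (Statistical analysis section): p0 = 0.40; p1 = 0.60; one-sided alpha 0.05; power 0.80; n1 = 21, continue if more than 8 respond; total n = 42, success if more than r = 22 respond; dropout 10%; planned total 47.

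**Formula.** Exact two-stage binomial, with futility stopping only at stage 1:

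P(success | p) = Σ over x = 9,…,21 of Bin(x; 21, p) × P[Bin(n − 21, p) > r − x]

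**Step 1: the plan's own figures.** With n = 42 and r = 22, P(success) is 0.0367 at p = 0.40 and 0.7976 at p = 0.60. The inflation is 42/0.9 = 46.7, rounded up to 47. Both reproduce, so the cut-off is calibrated to 42 analysed patients.

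**Step 2: the same cut-off on a larger FAS**, with 40% and 60% taken as rates in the FAS:

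| FAS size | Alpha, >22 | Power, >22 |
|---|---|---|
| 42 | 0.037 | 0.798 |
| 43 | 0.049 | 0.840 |
| 44 | 0.064 | 0.873 |
| 45 | 0.081 | 0.899 |
| 46 | 0.101 | 0.918 |
| 47 | 0.122 | 0.933 |

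Alpha passes 0.05 at 44 patients.

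**Step 3: the smallest cut-off that holds 0.05 at each size:**

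| FAS size | Cut-off | Alpha | Power |
|---|---|---|---|
| 42 | >22 | 0.037 | 0.798 |
| 43 | >22 | 0.049 | 0.840 |
| 44 | >23 | 0.035 | 0.808 |
| 45 | >23 | 0.047 | 0.847 |
| 46 | >24 | 0.033 | 0.817 |
| 47 | >24 | 0.044 | 0.854 |

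At 47, a cut-off of >23 would give alpha 0.077, so >24 is needed.

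**Step 4: the other reading of 40% and 60%.** Assumption, not in the article: these are rates among completers, and 10% of treated patients drop out and count as non-responders. The FAS rates are then 0.9 × 40% = 36% and 0.9 × 60% = 54%.

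| Rule | P(success) at 36% | P(success) at 54% |
|---|---|---|
| 47 patients, >22 | 0.042 | 0.764 |
| 47 patients, >24 | 0.011 | 0.590 |

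On this reading the stated cut-off at 47 holds alpha, with power just under four points short of 0.80.

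**The case against.** The strongest defence is that the design sentences, read alone, are ordinary: recruit 47 to obtain 42, and test at 42 with alpha 0.037 and power 0.798. The article never says that >22 is to be applied to 47. It also does not say how the 10% dropout splits before and after the first dose, and patients lost before dosing are outside the FAS. This stands in part. It means that 12% is one end of a range. It does not remove the conflict, because testing 42 evaluable patients would set aside treated dropouts whom the FAS definition keeps.

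Two stronger readings are tempting. A reader might infer that the test simply runs at 12%. That requires all 47 to be treated, the cut-off to stay at 22, and a true rate of 40% with dropouts included; the article does not fix all three. A reader might also infer that the design misses its stated properties however it is read. Step 4 shows otherwise: with completer rates, >22 at 47 gives alpha 0.042 and power 0.764.

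The final count is worded as if it might refer to stage 2 alone. That is no real ambiguity: stage 2 adds 42 − 21 = 21 patients, so a threshold of 22 can only be cumulative.

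It can also be said that this is a condensed article, that boundary adjustments are often left to an analysis plan, and that the Discussion calls the trial exploratory. Those facts limit the consequences. But the cut-off, the inflation and the analysis set are all stated in the same section and do not fit together, so the point is a conflict in the text and not a missing detail.

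**Conclusion.** The concern holds in this form: the only final cut-off is calibrated for 42 analysed patients, while the stated analysis set can contain up to 47. With >22 applied to the FAS and a true FAS rate of 40%, one-sided alpha lies between 3.7% and 12.2% for 42 to 47 patients and exceeds the stated 0.05 from 44 on.

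This rests on reading 40% and 60% as rates in the FAS. That is the more natural reading, since the null is stated for participants and the FAS is said to follow intention to treat, but the article does not say it outright. The calculation also assumes stage 1 is judged on 21 patients with the stated rule.

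**What to change.** State before the final analysis that 40% and 60% are FAS rates, with non-evaluable patients counted as non-responders. Keep the stage 1 rule. Give the final cut-off as a cumulative count over both stages, set by the actual FAS size: >22 for 42–43, >23 for 44–45, >24 for 46–47. Alpha is then at most 0.049 and power at least 0.798 across that range.

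The cost is wording only, with no extra patients. The downside is that up to two more responders are needed for success (25 instead of 23 at 46 or 47 patients).

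If 40% and 60% are meant as completer rates, the plan should say so, keep >22 at 47, and restate alpha as about 0.042 and power as about 0.76 under 10% treated dropouts counted as failures. The higher cut-off should not be adopted in that case: >24 at 47 would cut power from about 0.76 to about 0.59. The choice between the two readings therefore has to be written down first.
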